### Impact

Prior to the study’s commencement we developed a simple linear theory of change to guide our evaluation design. This can be seen in Fig. 1, in which different aspects of local PHT activity are theorised to contribute to changes to local alcohol licensing regimes, which in turn impacts on health and crimes outcome. Figure 2 adds some confounding factors to the theory. Using data collected during work package 1 we will revise and expand on this simple theory of change, producing a fuller list of activities, confounders and incorporating a systems lens.

**Fig. 1 Fig1:**
[figure not shown]
Simplified theory of change

**Fig. 2 Fig2:**
[figure not shown]
Simplified theory of change with major confounding variables and activity added

In developing the revised theory we will consider multiple mechanisms of action, some of which may be complementary and some competing, as well as feedback loops and adaptations in the licensing system resulting from different approaches to public health involvement. For example, some actions may focus on indirect mechanisms of action (influencing the nature and type of applications accepted e.g. licensed arts venues but not nightclubs [49]) whilst others may focus more directly on reducing the number of new licences granted through stronger licensing policy.

The emergent theory of change will be informed by practitioners’ views expressed in interviews, and detailed information on local licensing policy and decisions gathered via documentation analysis from WP 1 as well as outcome data from WP 2. The final theory (or theories) will be developed by the full study team, in consultation with the study advisory group and practitioners via a ‘stakeholder workshop’. We will invite all participating areas to attend this workshop at which we will present emerging findings and the draft theory of change.

### Dissemination

We will draw on our close links with PHE, AFS, the Alcohol Health Alliance, Alcohol Research UK, Cancer Research UK and others to ensure that our findings can influence local public health practice and national advocacy work. PHE host a National Public Health and Licensing Network (co-chaired by co-investigator [name]), whereas AFS host regular knowledge exchange events in Scotland for local teams, runs annual licensing conferences, and publishes a monthly e-newsletter. All of these organisations will disseminate study information and findings through established mechanisms and will guide us on appropriate formats for each audience. Our findings will also influence teaching and capacity building through annual alcohol policy courses delivered on behalf of the UK Centre for Tobacco and Alcohol Studies.

We expect to publish several peer-reviewed journal papers from each work package and will disseminate findings at UK and international conferences.

## Discussion

This study is important because alcohol is a major cause of health and social harms and regulation of its availability is a long-established mechanism for reducing those harms. Given the public health imperative to improve population health and wellbeing, there is a clear case for research designed to better understand how policy levers currently in place to influence alcohol availability are utilised by public health teams and what their impact may be. This research will help address acknowledged areas of uncertainty around whether and how current approaches to the regulation of alcohol availability are beneficial.

This natural experiment builds on the methodology and findings of recent work demonstrating an impact of licensing on health and crime outcomes [21, 28, 29], and will examine for the first time the effect, and mechanism of effect, of public health involvement in licensing. Using an interdisciplinary mixed-methods approach, and drawing on complex systems thinking, it will take into account the complexity of the relationship between public health activity, licensing decisions, and alcohol harms, as recommended in recent reviews [33–35]. It will involve in-depth examination of practice, acceptability and feasibility across two jurisdictions (England and Scotland) to build on earlier work [41, 44, 49, 51, 55, 66, 83].

The wide range of current public health practice will allow this study to generate qualitative contextualised data on the challenges and opportunities for PHTs seeking to affect alcohol-related harms through engagement with local premises licensing and will examine theories of change. At a local level, the study will be able to examine how public health teams can tailor their approaches to the licensing system to their local context, to maximise their likelihood of success, based on a clear theory of change.

As public health engagement in this area is potentially resource-intensive, findings from ExILEns will inform decisions on about whether this activity represents the best use of time for public health teams. If it is shown that there are measurable benefits, this will help to make the case for greater investment in public health capacity and/or potentially greater legislative support through the introduction of a public health objective in England. If, however, our findings suggest limited effects of public health activity in this arena, or little potential for licensing policy to materially affect alcohol-related harms, then this will contribute to current debate around more substantial legislative changes [84]. Should this study have null findings, this may, therefore, be as significant in policy terms as a demonstration of positive effects.

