### Power calculations

No quantitative data is available on the effect of public health engagement in licensing on alcohol-related harms. The assumed mechanism by which such engagement might reduce harms however, is by influencing the local licensing system. Statistical power estimations therefore have been based on effect sizes from two recent studies of the effect of alcohol premises licensing on alcohol-related hospital admissions and reported crime rates at the level of ‘lower tier local authority’ (LTLA) in England [28, 29]. Areas with active alcohol licensing policies had an average additional 2% (95% CI -3%:-2%) annual reduction in alcohol-related hospital admissions in the period up to and including 2013 compared to those without such policies [28]. Similarly, for the period up to 2013, an additional 4–6% annual decrease was seen in alcohol-related violent crimes, sexual crimes and public order offences in areas with active licensing policies compared to those with none [29].

We used the methodology developed by Edland for power calculations of linear mixed effects models with random slope [68]. Based on the previous studies, we conducted separate sample size calculations for alcohol-related hospital admissions and reported crime rates. For both analyses we assumed a standard level of statistical significance α (5%) and statistical power β (80%), and further assumed a 9-year follow-up (2009–2018) and a two-sided alternative. Table 4 outlines the detectable effect size with 20 intervention and 20 control areas.

**Table 4 Tab4:** Sample size data

	Expected average effect size %/year (slope)	Between-slope variance	Residual variance model	Number of areas in each group
*From previous study of impact of licensing on alcohol-related crime* [29]				
Crime rates^a^	−4.00% (−0.04)	0.003	0.03	29
	−5.00% (−0.04)	0.003	0.03	19
	−6.00% (−0.06)	0.003	0.03	13
*From previous study of impact of licensing on alcohol-related hospital admissions* [28]				
Rates	−2.31% (−0.229)	0.110	0.011	34
*Current study - minimum detectable effect size with proposed sample size*				
20 areas per group	−3.00% (−0.296)	0.110	0.011	20

^a^Effect size is a range between 4 and 6% as estimated by d Vocht et al. (2016) using quadratic trends

Based on Table 4, we expect the study to be able to detect effects on our outcomes within the range found in previous observational studies with 20 intervention and 20 control areas.

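### The Discussion gives null findings the same possible policy weight as positive ones, but on Table 4's inputs 20 areas per group has only about 59% power for the prior admissions effect and 59–64% for the lowest prior crime effect

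*Protocol article*

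**What the plan says.** The Power calculations section takes its effect sizes from two earlier studies of licensing policy, because no figures exist for public health engagement itself. For admissions the text gives an "average additional 2% (95% CI -3%:-2%) annual reduction in alcohol-related hospital admissions"; Table 4 uses −2.31%/year (slope −0.229). For crime the range is 4–6% a year. On method: "We used the methodology developed by Edland for power calculations of linear mixed effects models with random slope". The calculation uses 5% significance and 80% power, and "further assumed a 9-year follow-up (2009–2018) and a two-sided alternative".

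Table 4 lists 34 areas per group for the prior admissions effect, and 29, 19 and 13 per group for crime effects of −4%, −5% and −6% a year. With the planned 20 per group, its minimum detectable effect on the admissions variances is −3.00%/year (slope −0.296). The section concludes that "we expect the study to be able to detect effects on our outcomes within the range found in previous observational studies".

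The last paragraph of the Discussion says the findings will inform whether this work is a good use of public health teams' time. If they suggest limited effects of the activity, or "little potential for licensing policy to materially affect alcohol-related harms, then this will contribute to current debate around more substantial legislative changes". The next sentence is: "Should this study have null findings, this may, therefore, be as significant in policy terms as a demonstration of positive effects".

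**The concern.** The word 'therefore' in the closing sentence carries the reader from findings that suggest a limited effect to null findings, as though the second were an instance of the first. They differ. A null finding supports a limited effect only when the data are precise enough to rule out an effect that would matter. The article's power statement encourages the reader to assume that precision, while its own table shows it is lacking for admissions and for the smallest prior crime effect.

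If engagement worked exactly as well as licensing policy did in the earlier admissions study, a non-significant admissions result would still be quite likely. Read as the Discussion invites, that inconclusive result could be taken as evidence against the activity in a study meant to inform team resources and legislation.

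**Working it through.** **Inputs (all from Table 4 and the Power calculations text).** 20 areas per group; two-sided 5%; 80% target power. Admissions: slope variance 0.110, residual variance 0.011, prior slope −0.229. Crime: slope variance 0.003, residual variance 0.03, slopes −0.04 to −0.06. The spacing of time points is not stated, so I used 10 annual points (sum of squared deviations 82.5), 40 quarterly points (333.1), and slope variance alone.

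**Step 1: reproduce Table 4.** For a random-slope model,

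n per group = 2 × (1.960 + 0.842)² × [slope variance + residual variance / sum of squares] / slope².

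- Admissions, slope 0.229, annual points: 33.0 (Table 4: 34).
- Admissions, slope 0.296: 19.7 (Table 4: 20).
- Crime at 4%, 5%, 6%: 29.4, 18.8, 13.1 with slope variance alone; 30.3, 19.4, 13.5 with quarterly points (Table 4: 29, 19, 13). Annual points with the residual term give 33.0, 21.1, 14.7, which fits the crime rows less well.

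The method is therefore the plan's. The −5% crime row prints a slope of −0.04, but its 19 areas reproduce only with −0.05, which I use below.

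**Step 2: power at 20 per group.** SE of the slope difference = √(2 × [slope variance + residual variance / sum of squares] / 20); power = Φ(slope / SE − 1.96).

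Admissions: SE = √(2 × (0.110 + 0.011/82.5) / 20) = 0.105. Then 0.229/0.105 = 2.18, and Φ(2.18 − 1.96) = 0.588.

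Crime at −4%: SE = 0.0183 (annual), 0.0176 (quarterly) or 0.0173 (slope variance alone), giving power 0.587, 0.624 or 0.637.

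| Prior effect | Areas per group in Table 4 | Power at 20 | Missed |
|---|---|---|---|
| Admissions −2.31%/year | 34 | 59% | 41% |
| Crime −4%/year | 29 | 59–64% | 36–41% |
| Crime −5%/year | 19 | 78–82% | 18–22% |
| Crime −6%/year | 13 | 90–93% | 7–10% |

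Two cross-checks for admissions: scaling directly from the printed 34 gives Φ(2.802 × √(20/34) − 1.96) = 57.5%, and a t reference with 38 degrees of freedom gives 56.6%. At the 2%/year quoted in the text, with the slope scaled in proportion (an assumption), power is about 47%.

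**Step 3: what the interval can exclude.** The admissions 95% half-width is 1.96 × 0.105 = 0.206, and 0.206/0.229 = 0.90. The interval excludes the prior slope of −0.229 only if the estimate is above −0.229 + 0.206 = −0.023, that is, almost zero or unfavourable. If the true effect were exactly zero, the chance of that is Φ(0.023/0.105) = 59%. So even with no effect at all, about four times in ten the interval would still include the prior effect.

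**Step 4: smallest effect with 80% power at 20 per group.** Admissions: 2.802 × 0.105 = 0.294, in line with Table 4's 0.296 (−3.00%/year). Crime: 0.049 to 0.051, about −5%/year.

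**The case against.** A reader might infer that the plan adopts a rule that non-significance means no effect. The article does not say so. The sentence is closing Discussion prose, it says 'may', and it concerns policy significance. The two-sided 5% level appears as an assumption of the power calculation. The Analysis of primary outcomes section describes growth models, pre/post terms, difference-in-differences and a pre-specified plan, alongside several outcomes and qualitative work.

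A reader might also infer that no margin or interval criterion exists. Such a criterion could sit in an analysis plan that is not shown, so its absence from a journal article is not itself a fault.

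A third tempting reading is that the study would miss its prior effects about 40% of the time across the board. That is wrong for crime at −5% and −6%, and the figures above are for single outcomes in a two-group slope comparison, not the chance that the whole study is null.

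Finally, Table 4 openly prints the 34, the 29 and the −3.00%, and the detectability sentence is literally defensible: −3% is the outer limit of the quoted admissions interval, and −5% and −6% crime effects need no more than 20 areas.

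All of this stands, and it limits the point. What it does not answer is that the hedge never mentions an inconclusive result, and that the power sentence does not tell the reader which prior effects fall short.

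**Conclusion.** The point holds in limited form. The suggested reading of null findings and the general assurance of power are not supported by the plan's own table for admissions (power about 59%, missed about 41%) or for the lowest crime effect (power 59–64%, missed 36–41%). They are reasonably supported for crime at −5% and well supported at −6%.

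The figures rest on Table 4's variances as printed, on a comparison of slopes between 20 and 20 areas, on a normal approximation, and on the time spacings stated above. The admissions result hardly depends on spacing, because slope variance dominates. The article also assumes that engagement acts through licensing; if only part of its influence passes through, the true effect is smaller than the prior one and power is lower still. This is a matter of how results will be interpreted and how power is described; it does not call for a change of design or model.

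**What to change.** 1. In Power calculations, state that 20 areas per group gives about 59% power for the prior admissions effect of −2.31%/year and about 59–64% for a crime effect of −4%/year. Limit the detectability sentence to admissions effects of about −3%/year or larger and crime effects of about −5%/year or larger.

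2. In the Discussion, say that a limited effect on an outcome will be concluded only if the 95% confidence interval for the difference in slope excludes a pre-stated effect, and that a non-significant result whose interval includes that effect will be reported as inconclusive. The prior effects used in Table 4 are one possible reference. The choice is the investigators', since those effects concern licensing policy and not engagement, but it should be made before the outcome data are analysed.

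Both changes are wording only; the planned models can supply the interval. The cost is that fewer null results can be presented as policy-relevant, and a smaller reference effect would make that harder still.

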## Abbreviations

A&E: Accident and Emergency
AFS: Alcohol Focus Scotland
CIA: Cumulative impact area
DARS: Data Access Request Service
ExILEnS: Exploring the impact of licensing in England and Scotland
GMD: Generalised Mahalanobis Distance
HES: Hospital Episode Statistics
ISD: Information Services Division
LTLA: Lower tier local authority
NHS: National Health Service
NRS: National Records of Scotland
ONS: Office for National Statistics
PH: Public Health
PHE: Public Health England
PHT: Public health team
SAPM: Sheffield Alcohol Policy Model
SLP: Statement of licensing policy
WP: Work Package
